### Randomization and blinding

Each participating CHC will be assigned to either experimental group or control group by restricted randomization generated by an independent statistician, who works in the evidence-based center of FJTCM, via SAS software (Version 8.2, SAS Institute, Cary, North Carolina, United States). The random allocation sequence is blinded to the screeners who make the baseline test for the patients, and protected by a specified project manager who is not involved in the recruitment program of this study. Both allocation and baseline measurements will be concealed to outcome assessors.

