## Methods/Design

### Study design

The current study uses a multicentre, cluster randomized, parallel-controlled superiority design with blinded assessment (a flow diagram of the study design is presented in Figure 
1). The course of this trial will comprise a 4-week intervention and a 12-week follow-up period. The control group will receive SLT and initial therapies, while, the experimental group will receive additional scalp acupuncture. There is a total of five time points, including baseline, 2 weeks after treatment, 4 weeks after treatment, 6 weeks after follow-up, and 12 weeks after follow-up. Fujian University of Traditional Chinese Medicine (FJTCM), as an undertaker of this project, is responsible for completing the training of the rehabilitation therapists in a unified standard way before the study, and supervising their operations regularly during the study at all clinical sites. The Center of Evidence-based Medicine in FJTCM, which plays a role in randomization and will be blinded to the intervention, is an independent department employed to monitor and analyze data. The present project, funded by the State Administration of Traditional Chinese Medicine, has received approval from the local ethics committees of every center (Fujian: 2013KY-006-01, approval received in July 2013; Henan: 2014HL010, approval received in March 2014; Shandong: 2013KY-006-01, approval received in March 2014) participated in the study. Written informed consent is required prior to participation from each participant or their guardian, and they will be informed of the nature of this trial including its purpose, procedures involved, expected duration, potential risks and discomfort, as well as the possible benefits they will receive from it. There is no time limit for them to ask related questions and respond to the invitation to participate. Participants will be also informed that they are free to withdraw from the study at any stage for any reason and their personal information will be undisclosed and kept securely at FJTCM.

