### Participants and recruitment

The protocol will be carried out at community health centers (CHCs) run by three sub-centers, including the Affiliated Rehabilitation Hospital of Fujian University of Traditional Chinese Medicine (Fujian province, China), the Second Affiliated Hospital of Shandong University of Traditional Chinese Medicine (Shandong province, China), and the First Affiliated Hospital of Henan College of Traditional Chinese Medicine (Henan province, China). Many CHCs in different areas of the three provinces will be included in this protocol, providing a large number of patients.

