### Sample size

Referring to a trial
[23] with the same protocol as the present study, the effective rate of Broca’s aphasia after stroke was 64.71% in the control group (π_1_) and 85% in the experimental group (π_2_). Preliminary epidemiological findings show that there will not be less than 16 qualified participants recruited from each CHC. Prior data indicates that the intra-CHC correlation coefficient (ρ) is likely to be 0.030. Each group will consist of 132 individuals according to the formula:

(1)$$n=\frac{{\left(\mu_{\alpha }+\mu_{\beta }\right)}^{2}\;\left[\pi_{1}\;\left(1-\pi_{1}\right)+\pi_{2}\;\left(1-\pi_{2}\right)\right]\left[1+\left(m-1\right)\;\rho \right]}{{\left(\pi_{1}-\pi_{2}\right)}^{2}}$$

with a type I error of 5% (α = 0.05) and 90% power (β = 0.10). There will be 290 subjects included in total, allowing for a dropout rate of 10%.

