### Statistical methods

Statistical analysis in this study will be performed by a statistician who is not involved in this trial and works in the Center of Evidence-based Medicine in FJTCM. Analysis of all data will be conducted with SAS software (version 8.2, SAS Institute, Cary, North Carolina, United States), and two-sided *P* < 0.05 was considered statistically significant.

Descriptive statistics will be expressed in different forms according to the types of the data in each group. That is to say, continuous variables will use mean and standard deviation for normal distribution, with median and interquartile range for non-normal distribution, and categorical variables will use proportions with their standard error. Comparison of baseline characteristics, the primary or secondary outcomes between groups will use the *t*-test or Mann-Whitney test for continuous variables and Pearson chi-squared or Fisher’s exact test for categorical variables. Changes in effect sizes of primary or secondary outcomes from baseline to each time point for two groups will be expressed using the paired *t*-test or Wilcoxon signed-rank test.

The primary outcomes will be analyzed using full analysis set (FAS) and per protocol set (PPS), with the secondary outcomes using FAS. Analysis of the primary and secondary outcomes should be on the basis of the intention-to-treat (ITT) population. The safety set (SS) will be used to assess adverse events.

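### Health centres in three provinces are allocated by restricted randomisation, but the stated between-group tests carry neither the restriction factor nor the province, and they also ignore the health centre

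*Protocol article*

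**What the plan says.** Study design describes a "multicentre, cluster randomized, parallel-controlled superiority design with blinded assessment". Participants and recruitment adds that "The protocol will be carried out at community health centers (CHCs) run by three sub-centers", located in Fujian, Shandong and Henan. On allocation, Randomization and blinding says: "Each participating CHC will be assigned to either experimental group or control group by restricted randomization generated by an independent statistician". The article does not name the factor behind the restriction.

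Sample size allows for correlation within a CHC, through a factor 1 + (m − 1)ρ with m = 16 and ρ = 0.030. Statistical methods then fixes the comparison of primary and secondary outcomes between arms as the t-test or "Mann-Whitney test for continuous variables and Pearson chi-squared or Fisher’s exact test for categorical variables", two-sided at 0.05. None of these tests, as named, has a place for the restriction factor, the province or the CHC.

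**The concern.** An analysis should reflect how units were allocated. Here whole CHCs are allocated under a restriction and across three provinces, and the stated tests reflect none of that. What follows depends on the case.

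- **The tests as written.** Patients are treated as independent, so the standard error is too small. If provinces differ and were not balanced between arms, the excess of false positives grows.
- **An analysis repaired for the CHC, with a factor balanced by the allocation.** Variation between levels of that factor no longer affects the arm difference, but it stays in the error term. The test becomes conservative and loses power that the allocation had already secured.
- **Province not balanced.** With only about 18 randomised units, one arm may hold most of a province's CHCs, and nothing in the stated tests corrects for it.

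Province is a plausible source of variation. Study design dates ethics approval to July 2013 in Fujian and March 2014 in the other two provinces, and Trial status gives a November 2013 start, so province may also mark calendar time.

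**Working it through.** **Inputs from the article (Sample size).** π₁ = 0.6471, π₂ = 0.85, α = 0.05, power 90%, m = 16 (stated as a minimum), ρ = 0.030, 132 per arm, 290 in total.

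**Assumptions.** 18 CHCs (290/16 ≈ 18), 9 per arm, 6 per province. The article gives neither the number of CHCs nor any between-province variance, so a range is shown.

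**1. The plan's own figure.** The design effect is 1 + 15 × 0.03 = 1.45. The unpooled two-proportion formula gives 90.83 per arm, and 90.83 × 1.45 = 131.7, so 132 reproduces. For dropout, 264/0.9 ≈ 294 and 264 × 1.1 ≈ 291, both close to 290.

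**2. The tests as written.** Ignoring the CHC gives
- SE used / true SE = 1/√1.45 = 0.83
- true α = 2[1 − Φ(1.96/√1.45)] = 0.104

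Simulated α of the patient-level t-test (8,000 runs per case, ρ = 0.03 within province):

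| Province share of variance | Provinces balanced | Not balanced |
|---|---|---|
| 0 | 0.104 | 0.103 |
| 0.02 | 0.100 | 0.127 |
| 0.05 | 0.095 | 0.165 |
| 0.10 | 0.091 | 0.212 |

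With provinces balanced, the ratio of true to assumed variance is 1.45 × (1 − share). It falls below 1 only when the share exceeds 1 − 1/1.45 = 0.31.

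**3. After the analysis respects the CHC.** This uses a t-test on CHC means, with variance 0.03 + 0.97/16 = 0.0906 per mean. The effect is 0.48 SD, at which the plan's formula gives 90% power: √(2 × 3.2415² × 1.45/132) = 0.48. Degrees of freedom are 16 without province and 14 with it.

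Provinces balanced by the allocation:

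| Between-province SD | True α, no province term | Power, no term | Power, with term |
|---|---|---|---|
| 0 | about 5% | 88.7% | 88.0% |
| 0.1 | 4.3% | 87.1% | 88.3% |
| 0.2 | 3.1% | 81.4% | 88.2% |
| 0.3 | 2.1% | 71.5% | 88.2% |

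Provinces not balanced:

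| Between-province SD | Power, no term | Power, with term |
|---|---|---|
| 0 | 88.7% | 83.3% |
| 0.15 | 83.5% | 83.4% |
| 0.3 | 70.4% | 83.4% |

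These SDs come on top of ρ = 0.03. The total intra-CHC correlation is (0.03 + SD²)/(1 + SD²), which is about 0.04, 0.07 and 0.11 for SD 0.1, 0.2 and 0.3. If 0.030 is already the total, SD cannot exceed √0.03 ≈ 0.17, and the last two rows of the balanced table fall outside the plan's own figure.

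**4. Unlucky splits if province was not balanced.** Out of C(18,9) = 48,620 allocations, the chance of 3:3 in every province is C(6,3)³/48,620 = 16.5%. The chance that at least one province splits 5:1 or 6:0 is 28.0%. As one illustration, two provinces split 5:1 and 1:5 and differing by 0.3 SD shift the arm difference by 0.3 × (5/9 − 1/9) = 0.133 SD, or 0.133/0.48 ≈ 28% of the planned effect. That pair of splits has probability 6 × 6 × 6 × 20/48,620 = 8.9%.

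**The case against.** The strongest objection is that a reader might infer the planned tests to be conservative because a balanced factor is left out. The documents do not support that. The named tests also ignore the CHC, and at m = 16 and ρ = 0.030 this dominates: their standard errors are too narrow unless province explains about 31% or more of the variance, or nearly all of the stated correlation if 0.030 already includes province. The loss of power applies only to an analysis first repaired for clustering. This objection stands and shapes the conclusion.

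Four further objections stand in part.

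- **The variances are assumed.** No section gives a province effect, and Sample size does not say that ρ is a within-province figure. The two larger SDs may be too big. Unified training and regular supervision at all sites would tend to reduce province differences, and the article does not say that each province has separate staff.
- **The bias figure is one selected allocation.** Randomisation is unbiased on average, and a CHC-level test without province holds about 5% over all allocations. The harm lies in a particular unlucky allocation and in lost power. The 28% chance of a lopsided split is a wider event than the 8.9% case behind the 0.133 SD.
- **A province term can cost power.** If province was not balanced and provinces do not differ, power drops from 88.7% to 83.3%.
- **An article may leave details out.** A reader might take the unnamed restriction factor as an error. It is not, because a full protocol may name it, and province may already be balanced. Covariates are also often left to an analysis plan. But Statistical methods does name the tests, and those tests do not match the allocation described in the same article. That mismatch is what remains.

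**Conclusion.** The point holds as a mismatch between the stated allocation and the stated analysis. As written, the tests are anti-conservative: a standard error of about 0.83 of the true value and α of about 0.10 on the plan's own m and ρ. If provinces differ and were not balanced, α reaches 0.13 to 0.21 for province shares of 0.02 to 0.10.

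Repairing the clustering alone leaves a second gap. If the restriction balanced provinces, omitting province makes the standard error too wide, and power falls to between 87% and 72% against about 88% with the term, for an assumed SD of 0.1 to 0.3. Only SDs up to about 0.17 are compatible with 0.030 as a total correlation. If province was not balanced, there is a 28% chance that some province splits 5:1 or worse with nothing to correct for it, under the assumed 18 CHCs at 6 per province.

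The direction is firm. The size of the second part depends on a between-province variance and a number of CHCs that the article does not give.

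**What to change.** In Statistical methods, prespecify a between-group analysis that respects the CHC: either CHC-level summaries, or a model with a CHC random effect and a small-sample correction for about 18 clusters. Include as fixed effects the factor or factors actually used in the restricted randomisation, with province if it was one of them. In Randomization and blinding, for CHCs not yet allocated, balance the arms within province and include province in the analysis. For CHCs already allocated under another restriction, analyse by the factor that was used. The randomising statistician can supply it, and it should be fixed before outcomes are seen.

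The text change is a line or two in each section. Province uses 2 of about 16 degrees of freedom. Where provinces are balanced and do not differ, that costs under one point of power (88.7% to 88.0%). If province was not a restriction factor, adding it is optional: it costs up to about 5 points (88.7% to 83.3%) and pays only above a between-province SD of about 0.15.

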### Baseline tests

Baseline descriptive data will be obtained using a questionnaire consisting of the demographic data of subjects, such as gender, age, height, weight, nationality, education level, employment status, and information about stroke including the type, duration and location. All candidates will be tested on the severity of aphasia using the Boston diagnostic aphasia examination- Chinese version (BDAE-C). Broca’s aphasia is ascertained by CRRCAE. The functional condition of the brain is examined by using blood oxygen level dependent-functional magnetic resonance imaging (BOLD-*f*MRI) examination. Activities of daily life (ADL) will be reported with the Modified Barthel Index (MBI) and quality of life will be collected with the 36-Item Short Form Health Survey (SF-36).

### Intervention

Participants in the experimental group will receive integrated acupuncture therapy with SLT and initial therapies, meanwhile the control group will only receive SLT and initial therapy. The initial therapy consists of health education and conventional medical therapy. The treatments will take place five times per week for 4 weeks in total. All of the employees participated in this trial will be standardized in their training, including in the study protocol, methods of treatments, and assessments.

### Health education

For the purposes of improving patients’ knowledge of stroke and teaching them about the harmfulness of stroke and the necessity of treatment, patients admitted to hospital will be provided with access to educational brochures on stroke, which are based on the blueprint of ‘Freedom from the Misunderstanding of Stroke Rehabilitation’ (the first prize among popular science books from the Chinese Association of TCM)
[24]. Information about stroke in these brochures will include the concept, epidemiology, etiology and pathogenesis, risk factors, common symptoms, diagnosis, common complications, treatments, and precautions that should be taken. At the same time, rehabilitation physicians will introduce themselves and explain about the contents of the educational brochures to all participants in person.

### Conventional medical therapy

All participants will receive conventional medical therapies according to the Guidelines for the Prevention and Treatment of Cerebrovascular Disease in China (2007) published by the Chinese Medical Association
[25]. Specific treatments involve the interventions and management of the causes of disease, risk factors, and a range of comorbid conditions such as heart disease, diabetes, and hypertension.

### Speech and language therapy

During a retained time of the scalp acupuncture therapy, the experimental group patients will receive SLT which is based on the ‘Technical specification of Common rehabilitation therapy’ (2012) published by Chinese Association of Rehabilitation Medicine
[26]. The therapists will prescribe appropriate training programs, including different aspects of listening, speaking, reading, writing, or calculating and so on, on the evidence of each patient’s assessment result. Furthermore, the training’s degree of difficulty is based on every patient’s progress. The period of treatment will be continuous for 4 weeks at 5 days a week and 30 minutes per day.

### Scalp acupuncture therapy

The lower 2/5 of the anterior oblique line of vertex-temporal MS 6 (*Ding nie qian xie xian*) and anterior temporal line MS 10 (*Nie qian xian*) will be the needling sites. The anterior oblique line of vertex-temporal, which links EX-RN 1 (*Qian Si shen cong*) to GB 6 (*Xuan li*), is on the temporal side of the head and obliquely passes through the bladder and gallbladder meridians. The anterior temporal line is a part of the gallbladder meridian on the temporal side of the head, linking GB 4 (*Hanyan*) to GB 6 (*Xuanli*).

For correct manipulation, either a sitting or a dorsal position is appropriate. The area should be routinely sterilized before insertion of the needle. Number 30 Hwato needles of 0.30 mm in diameter and 40 mm in length (Suzhou Medical Appliance Factory, China) will be obliquely inserted (10 to 20° into the scalp) into the gales aponeurotica rapidly, then parallelly pierced 25 to 35 mm deep, along the lines described above, for point prescription. The acupuncture will be maintained for 30 minutes with rapid twirling performed for 2 to 3 minutes once 10 minutes, at a frequency of 180 to 300 twirls per minute. Each time after withdrawing the needle, a dry sterilized cotton ball should be pressed the puncture holes as quickly as possible to prevent bleeding. The therapy will be given once a day for 5 days a week lasting for 4 weeks continuously.

### Follow-up

There is a period of 12-week follow-up after the 4-week treatment. During this time trained personnel will call the participants and take a record every week, asking them something about their rehabilitation situation and whether they have received other treatments. Home visits will be at least once a month to assess their functional status including speech function, activities of daily living, and quality of life, using CRRCAE, BDAE-C,MBI, and SF-36 after 6 and 12 weeks follow-up.

### Outcome measures

Except for baseline (-2 to -1 weeks), all of the primary and secondary outcomes assessment will be also conducted at end of 2-week treatment (3 weeks), end of 4-week treatment (5 weeks), end of 6-week follow-up (11 weeks), and end of follow-up period (17 weeks) with a BOLD-*f*MRI examination only at end of the 4-week treatment (5 weeks). A summary of all the measures in the trial is shown in Table 
1.

**Table 1 T1:** Trial processes chart

**Items**		**Before enrolment (weeks) -2 to (-1)**	**Intervention period (weeks) 1 to 2**	**End of 2-week treatment (weeks) 3**	**Intervention period (weeks) 3 to 4**	**End of 4-week treatment (weeks) 5**	**Follow-up (weeks) 5 to 10**	**End of 6-week follow-up (weeks) 11**	**Follow-up (weeks) 11 to16**	**End of 12-week follow-up (weeks) 17**
Recruitment		**×**								
Enrolment		**×**								
Inclusion criteria		**×**								
Exclusion criteria		**×**								
Informed consent		**×**								
Basic characteristic variables		**×**								
Randomization and allocation concealment		**×**								
Primary outcomes	Speech function	**×**		**×**		**×**		**×**		**×**
	Severity of aphasia	**×**		**×**		**×**		**×**		**×**
Secondary outcomes	Activities of daily life	**×**		**×**		**×**		**×**		**×**
	Quality of life	**×**		**×**		**×**		**×**		**×**
	Functional condition of the brain	**×**				**×**				
Adverse events recorded			**×**		**×**		**×**		**×**	
Self-reported drug therapy			**×**		**×**		**×**		**×**	
Cost sheet of rehabilitation therapy			**×**		**×**		**×**		**×**	

### Primary outcomes

The primary outcome measures in this study are the differences in the scores on both the CRRCAE and the aphasia grading standard of severity in BDAE-C after intervention and follow-up between the two groups and within groups.

The CRRCAE
[27,28] was made by Chinese Rehabilitation Research Center with the help of Japanese experts according to Chinese language and cultural habits by referring to the Japanese Standard language Test of Aphasia (SLTA). It consists of two parts. One part includes twelve questions about demography date and is used to test the patients’ general condition of speech. The other part contains nine subtests (auditory comprehension, repetition, speaking, reading aloud, reading comprehension, copying, description, dictation, and calculation). There are 30 quizzes in total, with three or four quizzes in each subtest. This scale has been used widely in hospitals and rehabilitation centers in China with a good reliability and validity. The interclass correlation coefficients (ICC) of test-retest reliability exceeded 0.9, the Cronbach’s α of internal consistency was 0.941, and the relationship with the Western Aphasia Battery (WAB) was 0.948 (on aphasia quotients). Furthermore, we can diagnose whether a person has aphasia and, if so, the degree of severity from the result of CRRCAE which can guide the strategies of therapy and can also measure the outcomes of treatment.

BDAE
[29] is a widely used aphasia examination in the world. As the BDAE original edition is not suitable for Chinese conditions, it was revised to BDAE-C
[30,31] based on the Chinese culture and language background, and is now established as the standard for Chinese patients. There are six grades in the aphasia grading standard of severity in BDAE-C from the worst to the best in the order of 0 to 5.

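### The primary outcome fixes neither a time point nor a success rule for its two instruments, and it counts within-group change as primary

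*Protocol article*

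**What the plan says.** The protocol article, Primary outcomes, names score differences on CRRCAE and on the BDAE-C severity grade as the primary measures, taken "after intervention and follow-up between the two groups and within groups".

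Outcome measures says that the primary and secondary outcomes are assessed, apart from baseline, on these occasions: "end of 2-week treatment (3 weeks), end of 4-week treatment (5 weeks), end of 6-week follow-up (11 weeks), and end of follow-up period (17 weeks"; only the fMRI is limited to one post-baseline time. Table 1 marks both primary measures at all four post-baseline visits.

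Statistical methods sets one threshold, "two-sided *P* < 0.05 was considered statistically significant". For comparisons between arms, "the primary or secondary outcomes between groups will use the *t*-test or Mann-Whitney test for continuous variables". Change within each arm "from baseline to each time point for two groups will be expressed using the paired *t*-test or Wilcoxon signed-rank test".

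Sample size takes a type I error of 5% and 90% power for a single comparison of a binary effective rate, 64.71% against 85%.

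**The concern.** Study design describes a superiority trial, so the primary outcome should point to a between-group comparison that decides the question. Three things in the definition prevent that.

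- **Time.** The primary outcome is placed after intervention and follow-up, with four post-baseline visits on the schedule and none singled out.
- **Instruments.** Two are named, without saying whether success on one is enough.
- **Within-group change.** It is given the same standing as the between-group difference. Both arms receive speech and language therapy (Intervention), and the Discussion concedes that spontaneous recovery cannot be removed as a confounder. Improvement from baseline in the acupuncture arm is therefore expected even if acupuncture adds nothing.

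The Abstract and the Discussion say that, if the result is positive or the project successful, the technique could be implemented on a large scale in China and worldwide. With the definition as written, what counts as positive could be settled after the results are seen.

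**Working it through.** **1. The plan's own figure.** Sample size gives π₁ = 0.6471, π₂ = 0.85, m = 16, ρ = 0.030, α = 0.05 and power 90%. The design effect is 1 + 15 × 0.030 = 1.45. Taking α two-sided:

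n = (1.960 + 1.282)² × [0.6471 × 0.3529 + 0.85 × 0.15] × 1.45 / (0.85 − 0.6471)² = 131.7, so 132 per group.

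This matches the stated 132, and 264 × 1.10 = 290.4 matches the stated total of 290. The calculation covers one 5% test of a binary rate. It is not a calculation for either score.

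**2. Counting the comparisons.**
- Between groups, all four visits: 2 instruments × 4 times = 8.
- Between groups, only end of treatment and end of follow-up: 2 × 2 = 4.
- Within groups, at each time point: 2 instruments × 4 times × 2 arms = 16.

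**3. Chance of at least one false-positive between-group result, 5% per test, tests independent.**
- Eight tests: 1 − 0.95⁸ = 0.337.
- Four tests: 1 − 0.95⁴ = 0.185.

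**4. The same with correlated tests, and under a both-must-succeed rule.** Repeated scores on the same patients are positively correlated, so the independent figures are upper ones. The article gives no correlations; those below are assumptions. The results come from multivariate-normal simulation of 2 instruments × 4 times under no treatment effect, with each test statistic behaving as a valid standard normal.

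| Assumed correlation (between times / between instruments) | Any of 8 tests | Any of 4 tests (two times) | Both instruments, same direction and same time, any of four times | Same rule, two times |
|---|---|---|---|---|
| 0.7 / 0.7 | 21% | 14% | 5% | 3% |
| 0.8 / 0.8 | 17% | 12% | 5% | 4% |
| 0.9 / 0.8 | 14% | 11% | 4% | 3% |

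If both instruments must succeed at one named time, the chance cannot exceed 5%, because it cannot exceed the chance for either test alone. That cap holds whatever the correlation. The roughly 3–5% over several times holds only for the assumed values.

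**5. Within-group change.** Suppose both arms improve by 0.3 standard deviations of the change score for reasons unrelated to acupuncture (an illustrative value). With 132 per arm, the power of a paired test, ignoring clustering, is Φ(0.3 × √132 − 1.96) = Φ(1.487) = 0.93. A significant paired result in the acupuncture arm would be the likely finding under no acupuncture effect.

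**The case against.** **Both instruments are named, so they may be co-primary.** This is a fair reading, and it largely removes the error-rate problem, as the last two columns of the table show. But the article does not state that both must succeed, and the time point would still be open.

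**The outcome may refer to two times, not four.** The wording allows this. The Abstract and the Discussion describe the five assessment points as a way to follow the course of the effect, and the phrase about each time point in Statistical methods belongs to the paired tests, not to the between-group tests. Eight between-group tests is therefore one reading. Four is another, and it still leaves 11–14% if any one success suffices.

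**Multiplicity rules belong in the statistical analysis plan.** This stands. The absence of an alpha adjustment or a testing hierarchy in a condensed article is not held against it. The choice of primary outcome is a protocol matter, however, and here the text itself spreads it over two instruments and an open set of times and adds within-group contrasts.

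**A reader might infer that any one significant test makes the trial positive, so that its type I error is 34%.** The article states no such rule, and 34% also requires independent tests.

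**Conclusion.** The primary outcome is wrongly specified in three respects: no time point, no rule for the two instruments, and within-group change counted as primary. The third is wrong on any reading. The effect of the first two depends on the missing rule: 34% for eight independent tests (about 14–21% correlated) or 18.5% for four (about 11–14% correlated) if one success is enough, and about 3–5% if both instruments must agree in direction at the same time. The correlated figures rest on assumed correlations of 0.7 to 0.9.

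Two further inferences are not supported here. One is to raise these rates by the design effect of 1.45. Ignoring clustering in the analysis is a separate matter that naming one test would not cure, and the article gives no intra-center correlation for either score. The other is to quote a joint power for the two instruments. The 90% belongs to the binary effective rate, and no effect size or standard deviation is given for CRRCAE or BDAE-C.

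**What to change.** 1. Delete the within-group part from the primary outcome. Report change from baseline in each arm descriptively, without P values.
2. Before unblinding, name one between-group primary time point. The end of the 4-week treatment (week 5) is one acceptable choice; the end of follow-up could also be defended, since the Discussion stresses long-term stability.
3. State the success rule: either one lead instrument (for example CRRCAE, with BDAE-C tested next in a fixed sequence at the same time) or two co-primaries that must both succeed.
4. Make the remaining times secondary, to describe course and durability.
5. Reconcile the sample size with the chosen primary score. Until that is done, the power for that score is unknown.

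Items 1 to 4 are changes of wording, and every assessment stays. The price is that only the named comparison carries the confirmatory claim. Item 5 takes more work, because it needs an effect size and a standard deviation that the article does not give.
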